### Qualitative study in LAP-PIE trial

A qualitative study will be carried out to understand patients’ and clinicians’ perspectives and experiences of the procedure and the design of the trial. All patients approached to participate in the trial will be invited to participate. A purposive sample of healthcare professionals involved in the trial will also be invited. Trial nurses, local R&D (research and development) personnel and Network CRN (clinical research network) managers will be included. This information will be gathered via interviews by an experienced qualitative researcher.

Interviews will be transcribed verbatim and managed using computer-assisted qualitative data analysis software (iNVivo).^33^ Emerging data will be used to modify trial information and protocol. This may include the development of training materials for staff and changes to participant information sheets.

### Translational study

A translational substudy will evaluate prognostic markers for outcome. Imaging prior to and during IRE therapy will be correlated with outcome as will the immune response to IRE therapy by assessing circulating immune responses (including absolute lymphocyte count, eosinophils, neutrophil: leucocyte ratio, Tregs and IFNγ at baseline, 6 hours and 6 days post-therapy.

### Progress to full trial

The criteria to progress to a subsequent full trial will be determined quantitatively as (A) the ability to recruit 50 patients to the study across the study sites (B) a consent rate of 20±11%, (C) overall technical success rate of 50±14% and (D) a loss to follow-up of 10±8%.

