## Methods and analysis

### Study design and setting

The LAP-PIE trial is a UK multicentre feasibility study that will recruit 50 patients with LAPC in whom the disease has remained localised and unresectable following FOLFIRINOX. Patients will receive 3–6 months of FOLFIRINOX prior to restaging and being assessed for study eligibility. All participants will be offered palliative chemotherapy according to standard centre protocols and half will also be offered one IRE procedure. If new agents for second-line therapy are approved by NICE prior to or during the LAP-PIE trial, these can be offered in the second-line chemotherapy arm and following IRE therapy if considered appropriate by the treating oncologist. Patients randomised to the control arm who have benefitted from initial chemotherapy with FOLFIRINOX may continue on the same regimen if this deemed appropriate by the treating oncologist. It is an open-label study. Patient enrolment is expected to last 15 months assuming a recruitment rate of 0.8 patients per site per month across seven UK centres and an opening site rate of 0.5 per month. The trial will be conducted in specialist pancreas cancer centres. IRE will be delivered across all trial centres. Interventional radiologists performing pancreas IRE in the trial will have performed a minimum of five previous pancreas or liver IRE ablations prior to administrating IRE to participants enrolled in the trial. Additional technical support will be available from manufacturers of the equipment, AngioDynamics. Figure 1 summarises the trial design and table 1 demonstrates the schedule of enrolment, interventions and assessments.

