### Outcomes

The primary objective of the LAP-PIE trial is to ascertain feasibility of such a trial concept. In particular, the ability to identify and recruit LAPC patients at the selected sites to the LAP-PIE trial will be evaluated. The primary outcome consists of recruitment rate, number of screening failures, number of patients completing study pathway as per protocol and trial withdrawal rate.

The secondary objectives of the LAP-PIE trial aim to assess the practicality and technical success rate of pancreas IRE treatment. Technical success will be determined by the interventional radiologist performing the procedure. The procedure will be deemed to be technically successful if the entire tumour has been treated based on imaging performed during the intervention. Completion and complication rates of IRE procedures will be evaluated. The proportion of patients in whom percutaneous IRE was successful, defined as no local growth on follow-up, will be determined as will the proportion of patients who became eligible for surgery following IRE and the R0/R1 resection rates in these participants. Acceptability of pancreas IRE therapy to patients and their clinicians, rate of withdrawal from the study and outcome measures including OS (measured from randomisation), PFS and QoL will be evaluated. Finally, health-related costs, including indicative costs related to health resource use in both arms, social costs of attending IRE treatment such as cost of travel to and from a tertiary centre, time off work and social support costs will be evaluated.

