### Sample size calculation

Formal sample size calculations are not appropriate for a feasibility study. Sample sizes between 24 and 50 have been recommended to estimate the SD required for a sample size calculation to allow for the design of a subsequent RCT aimed at evaluating the cost-effectiveness of IRE in patients with LAPC.^29 30^ A convenient sample size of 50 patients, randomised equally to the two groups, has been selected.

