### Assessment of feasibility

One aspect of the feasibility evaluation of this trial is to evaluate the ability to recruit patients with LAPC into a trial of this nature. The average number of patients with unresectable LAPC within UK specialist pancreas units is 60 patients per centre per year (Royal Free Hospital London audit data 2017, unpublished). Staging following FOLFIRINOX chemotherapy will demonstrate localised but unresectable disease in approximately 40 out of 60 patients (65%).^12^ These patients will be eligible for the LAP-PIE trial. We anticipate recruiting 20% of potential participants to the LAP-PIE trial, which equates to eight per centre per year. Recruitment within five centres would allow 40 UK patients per year. A recruitment time of 15 months would allow 50 patients to be recruited.

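### The progression margins for technical success and consent appear to use 50 as the denominator, which fits neither: expected precision is about ±20 points (not ±14) and about ±5 points (not ±11)

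*Protocol article*

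**What the plan says.** Under Progress to full trial, the protocol article lists four quantitative criteria for moving to a full trial. The first is recruiting 50 patients. The other three are rates with margins, in per cent: "B) a consent rate of 20±11%, (C) overall technical success rate of 50±14% and (D) a loss to follow-up of 10±8". That section says neither what each rate is a proportion of nor what the ± sign means.

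The denominators have to come from other sections:

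- Sample size calculation: "A convenient sample size of 50 patients, randomised equally to the two groups, has been selected".
- Study design and setting: of all participants, "half will also be offered one IRE procedure".
- Outcomes: "The procedure will be deemed to be technically successful if the entire tumour has been treated based on imaging performed during the intervention".
- Assessment of feasibility: "We anticipate recruiting 20% of potential participants to the LAP-PIE trial, which equates to eight per centre per year". The same section takes about 40 eligible patients per centre per year, five centres and 15 months.

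**The concern.** The three rates are measured on three different groups of patients, yet their margins look as if one sample size was used for all of them. Controls have no IRE procedure to rate, so technical success cannot be estimated on all 50. Consent is measured on those who could have joined, and the 50 recruits are its numerator. If 50 were the denominator, 20% consent would give 10 recruits, against the 50 that the first criterion requires.

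These figures are the stated quantitative basis for deciding on a full trial. A reader planning that trial would take technical success to be known more precisely than the design allows, and consent less precisely.

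**Working it through.** **Inputs.** 50 patients randomised equally, so 25 per arm (Sample size calculation; Study design and setting). Technical success is judged on imaging during the IRE procedure (Outcomes). Planned rates are 20%, 50% and 10% (Progress to full trial). The recruitment projection uses 40 eligible patients per centre per year, five centres and 15 months (Assessment of feasibility). Seven centres opening at 0.5 per month are given in Study design and setting. Assumed: two-sided 95% level, z = 1.96.

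**Formula.** Half-width = 1.96 × √(p(1−p)/n).

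**Reproducing the stated margins with n = 50**

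- Consent: 1.96 × √(0.20 × 0.80/50) = 11.1 points (stated 11).
- Technical success: 1.96 × √(0.50 × 0.50/50) = 13.9 points (stated 14).
- Loss to follow-up: 1.96 × √(0.10 × 0.90/50) = 8.3 points (stated 8).

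All three round to the stated values. The alternatives tried do not reproduce all three: 90% with n = 50 gives 9.3, 11.6 and 7.0; 95% with n = 25 gives 15.7, 19.6 and 11.8; 80% with n = 25 gives 10.3, 12.8 and 7.7. Solving the rounded margins for n at 95% gives about 46 to 56, 46 to 53 and 48 to 62. All three ranges contain 50.

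**Technical success on its own denominator**

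- n = 25: 1.96 × √(0.25/25) = 19.6 points, or about 30% to 70% (Wilson interval 31.8% to 68.2%).
- n = 20, if five patients are not treated: 1.96 × √(0.25/20) = 21.9 points.

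**Consent on its own denominator**

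- From the target: 50/0.20 = 250 potential participants.
- From the projection: 5 × 40 × 15/12 = 250.
- n = 250: 1.96 × √(0.16/250) = 4.96 points, or about 15% to 25%.
- Seven centres open throughout: 7 × 40 × 15/12 = 350, giving ±4.2 points.
- Seven centres with one opening every two months from month 0 (an assumed pattern at the stated rate): 15 + 13 + 11 + 9 + 7 + 5 + 3 = 63 site-months; 63 × 40/12 = 210, giving ±5.4 points.

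The stated ±11 is therefore about 11.1/4.96 = 2.2 times too wide as a 95% precision.

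**Loss to follow-up.** This is measured on the 50 randomised, so ±8 stands.

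**The case against.** The strongest reply is that the section calls these figures criteria, not confidence limits. An acceptance band need not equal a 95% half-width, and the section states no level. That is fair, and the precision reading remains an inference. Still, three margins matching one formula at one sample size is hard to explain otherwise. If they are acceptance bands, their widths appear to come from a calculation that fits only one of the three rates.

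The second reply is that the article never gives a consent denominator. That also stands. It gives a share of potential participants and does not say how many will be approached. If only some eligible patients are approached, 50 recruits would be more than 20% of a smaller number. The 250 is therefore an assumption, with 210 to 350 as a reasonable range. Nowhere in that range does the margin come near ±11.

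A reader might infer that the wide consent band could let the project go forward on poor consent. The article does not support that. The criteria are joined, and the first requires 50 recruits. On a pool of 250, 9% consent gives about 22 recruits (0.09 × 250 = 22.5) and fails. Reaching 50 recruits at 9% would need about 556 potential participants (50/0.09). A floor below the planned rate is also not an error in itself.

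A reader might also want to put the recomputed half-widths in place of the bands. As a decision rule, 50 ± 20 would move the technical-success floor from 36% (50 − 14) to 30% (50 − 20), making progression easier because fewer patients are measured. Likewise, 20 ± 5 would put a 30% consent rate outside the band. Precision and threshold have to be kept apart.

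**Conclusion.** Wrong as written, and it should be fixed. Read as 95% precisions, two of the three margins conflict with the article's own design. Technical success has about ±20 points on at most 25 patients, against ±14 stated. Consent has about ±5 points on about 250 potential participants (±5.4 to ±4.2 for 210 to 350), against ±11 stated. Loss to follow-up is correct.

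The conclusion rests on two inferences: that ± means a 95% normal-approximation half-width, and that the consent denominator is the pool of potential participants. The technical-success denominator needs no such inference, because it follows from the allocation and the definition of the outcome.

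The finding goes no further than these two margins. The planned rates, the recruitment criterion, the sample size of 50 and patient safety are unaffected. The Sample size calculation section needs no change, because it justifies 50 by the estimation of a standard deviation and not by the precision of these rates.

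**What to change.** In Progress to full trial:

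1. Name the confidence level and the denominator for each rate.
2. Restate the expected 95% precision: consent 20% ± 5 points (assumed n of about 250; ±5.4 to ±4.2 for 210 to 350), technical success 50% ± 20 points (n = 25 or fewer), loss to follow-up 10% ± 8 points (n = 50).
3. State the progression thresholds separately, as one-sided limits: a minimum for consent, a minimum for technical success and a maximum for loss to follow-up. The wider interval for technical success then does not lower the bar, and better-than-expected results do not fall outside a band.

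The cost is a change of wording plus a decision by the trial team on the three limits, best made before the criteria are applied. No extra patients or data are needed.

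### Progression criteria B to D are two-sided windows with no favourable direction, so read literally some clearly better results fail; the low part of the consent window is also out of line with the 50-patient target

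*Protocol article*

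**What the plan says.** The section *Progress to full trial* introduces a numerical rule: "The criteria to progress to a subsequent full trial will be determined quantitatively as (A) the ability to recruit 50 patients". Criterion A is "A) the ability to recruit 50 patients to the study across the study sites", with no time limit attached. The other three are a central value with a half-width, all in per cent: "B) a consent rate of 20±11" and "C) overall technical success rate of 50±14% and (D) a loss to follow-up of 10±8". No minimum, maximum or governing edge is given there or elsewhere in the article.

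The section *Assessment of feasibility* derives the target of 50. It takes about 40 eligible patients per centre per year and 20% recruited, "which equates to eight per centre per year", over five centres and 15 months. The abstract and *Study design and setting* allow up to seven centres over the same 15 months. The latter assumes 0.8 patients per site per month and sites opening at 0.5 per month. *Sample size calculation* randomises 50 patients equally, so about 25 are allocated to IRE. *Outcomes* defines technical success on the IRE procedure, so only those patients can contribute to criterion C.

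**The concern.** For each of the three criteria one direction is plainly good: more consent, more technical success, fewer patients lost. A window that closes on both sides ignores this. Taken at its word, it turns away a trial in which nearly every tumour was fully treated or nobody was lost, and it passes one with middling results. If the oversight groups set the rule aside when that happens, the decision is no longer prespecified.

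The unfavourable side is equally unclear. Technical success of 40%, or loss to follow-up of 15%, passes if the windows are the rule and misses if 50% and 10% are the targets. Finally, the lowest consent that B accepts does not deliver the recruitment that A asks for in the planned period.

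The trial exists largely to inform whether a full randomised trial should follow, and this paragraph is its stated rule for doing so.

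**Working it through.** **1. Reproducing the plan's recruitment figure.** Eligible per centre-year × consent × centres × years: 40 × 0.20 × 5 × 15/12 = 50. This agrees with the article. The eligible pool is 40 × 5 × 1.25 = 250 patients.

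The seven-centre figure also reproduces if the first site opens at month 0 and one more opens every two months: 15+13+11+9+7+5+3 = 63 site-months, and 63 × 0.8 = 50.4.

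**2. Where the half-widths come from.** 1.96 × √(p(1−p)/n) with n = 50:
- p = 20%: 11.1 points (stated ±11)
- p = 50%: 13.9 points (stated ±14)
- p = 10%: 8.3 points (stated ±8)

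All three match, so these look like 95% precision figures on 50 patients. Only loss to follow-up has 50 as its natural denominator. For technical success n is about 25, giving ±19.6 points. For consent n is about 250 eligible patients at five centres, giving ±5.0 points.

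**3. Criterion C read literally.** With n = 25, 36–64% means 9 to 16 successes. Exact binomial:

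| True technical success | Chance of passing | Chance of failing as too high |
|---|---|---|
| 40% | 72% | – |
| 50% | 89% | 5% |
| 60% | 72% | 27% |
| 70% | 32% | 68% |
| 80% | 5% | 95% |

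The window is symmetric about one half, so it cannot tell a true rate of 40% from one of 60%.

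**4. Criterion D read literally.** With n = 50, 2–18% means 1 to 9 losses, so 0/50 fails. The chance of 0/50 is 0.99^50 = 61% if true loss is 1%, and 0.98^50 = 36% if it is 2%. At a true loss of 10% the chance of passing is 97%.

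**5. Criterion B against criterion A.** Patients recruited in 15 months at 40 eligible per centre-year, and the consent needed for 50:

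| Site model | Yield at 9% | Yield at 20% | Consent needed for 50 |
|---|---|---|---|
| Five centres | 250 × 0.09 = 22.5 | 50 | 50/250 = 20% |
| Seven, all open from the start | 350 × 0.09 = 31.5 | 70 | 50/350 = 14.3% |
| Seven, opening in stages (63 site-months) | 210 × 0.09 = 18.9 | 42 | 50/210 = 23.8% |

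Fifty patients at 9% consent would need 50/0.09 ≈ 556 eligible patients. With no time limit that takes 33.3 months in five centres or 23.8 months in seven centres all open.

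**The case against.** The strongest reply is that the ± values were never meant as acceptance windows: they are expected values with their precision, and nobody would stop a programme because 80% of procedures succeeded. Step 2 makes that origin likely, and no section says that a better result would block progression. The failure probabilities in steps 3 and 4 therefore apply only to the literal reading. But the precision reading does not rescue the paragraph. It leaves a rule described as quantitative with no go or stop line for B, C or D, and the precision is computed on the wrong denominator for two of the three.

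A reader might infer three stronger things that the article does not support.
- *That any better-than-planned result fails.* Most do not: technical success of 51–64%, consent of 21–31% and loss of 2–9% all lie inside the windows.
- *That A and B contradict each other.* They can be met together, for example at 20–31% consent in five centres. If all four criteria must be met, low consent within 15 months is caught by A.
- *That A is unreachable at low consent, or needs the full 20%.* That holds only for five centres over 15 months. With seven centres all open 14.3% suffices, and A itself has no time limit.

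This is also a condensed article, and the full protocol may give a direction. The article, however, does state the rule, and states it in a form that cannot be applied sensibly.

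**Conclusion.** The point holds. As published, criteria B to D have no favourable direction. Read literally they fail 17/25 or more technical successes, 0/50 lost and consent above 31%, while passing poorer results such as 40% technical success. Read as precision they contain no decision threshold. Either way the paragraph needs rewriting before data are seen.

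The misalignment of B with A is a matter of degree. At 9% consent the planned 15 months yields about 19 to 32 of the 50 patients in every site model that the article supports. The consent that does deliver 50 is between 14.3% and 23.8%.

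These figures assume 25 patients assessed for technical success, 50 for loss to follow-up, about 40 eligible patients per centre per year, all of them approached, and, in the staged model, a first site opening at month 0. Enrolment, randomisation and estimation are not affected.

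**What to change.** Before any outcome data are seen, rewrite the paragraph as follows.

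1. Make B to D one-sided: a minimum for consent, a minimum for technical success and a maximum for loss to follow-up. Delete the favourable edges.
2. Name each denominator: eligible patients approached for B, patients assessed for IRE technical success for C, and patients randomised for D.
3. Set a go line, a stop line and an amend-and-review zone between them. One option uses the planned value as the go line and the unfavourable edge, on the right denominator, as the stop line. That gives consent 20% and 20 − 5.0 = 15.0%; technical success 50% and 50 − 19.6 = 30.4%; loss to follow-up 10% and 10 + 8.3 = 18.3%. The exact lines are for the oversight groups to choose.
4. State the site and time model behind A, and set the consent minimum to agree with it: 20% for five centres, 14.3% for seven all open, or 23.8% for seven opening in stages. The 15.0% in item 3 is compatible with A only in the second of these, so the groups must also say whether A has an amend zone or a time limit.

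The cost is one rewritten paragraph agreed by the oversight groups, with no extra patients or data. The downside is that the precision for technical success is shown to be wider than the article implies. With 25 patients, a 50% go line requires 13 successes and would be missed half the time if the true rate were exactly 50%, which is why the middle zone is needed.

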### Ethics

The trial will abide by the principles of the World Medical Association Declaration of Helsinki and has approval from London Brent Research Ethics Committee, reference number 21/LO/0077. The trial has been registered on International Standard Randomised Controlled Trial Number https://doi.org/10.1186/ISRCTN14986389.

### Publication and dissemination

Results from different centres will be analysed and published together following completion of the recruitment and follow-up period. This will be presented to an international conference with an interest in hepatopancreaticobiliary surgery, oncology and IR and published in a peer-reviewed journal.

## Discussion

### Trial justification

Local ablative therapy using IRE in patients with LAPC has been shown to be beneficial in prospective and retrospective studies (median survival 27 months);^14^ however, the increase in survival reported may be due to patient selection for IRE rather than the effect of IRE (selection bias). A systematic review of IRE therapy in LAPC included retrospective and prospective studies but no RCTs.^14 34^ Moreover, the heterogeneity among individual trial participants including varying concomitant treatments prevented combination of data sets making it difficult to establish the true impact of IRE. Despite this, the systematic review is a useful aid in summarising findings including complication rates following IRE and highlighting the current knowledge gaps such as the relationship between number of procedures performed and outcome and the impact of IRE on QoL.

A study using PSM reported a median OS of patients with LAPC undergoing IRE of 21 months,^13^ similar to that reported by the systematic review (27 months).^14^ Such a study may effectively adjust for observed variables between cohorts and can contribute to a more precise estimation of treatment response. However, selection bias cannot be completely eliminated because PSM does not adjust for unobserved differences between groups. In order to address selection bias, a well-designed randomised control trial is required.

Before IRE can be justified by NICE to be incorporated into routine clinical practice, a randomised control trial is needed evaluating the benefit of IRE in addition to standard of care chemotherapy, which in the UK is FOLFIRINOX. While a larger trial is required to investigate IRE treatment in LAPC, patients and clinicians may not be willing to enter the trial and, therefore currently a large RCT is justified but not feasible.

